## Abstract

**Background:**

Since 2010, the Ovation Abdominal Stent Graft System has offered an innovative sealing option for abdominal aortic aneurysm (AAA) by including a sealing ring filled with polymer 13 mm from the renal arteries. In August 2020, the redesigned Ovation Alto, with a sealing ring 6 mm closer to the top of the fabric, received CE Mark approval.

**Objective:**

This registry study aims to evaluate intraoperative, perioperative, and postoperative results in patients treated by the Alto stent graft (Endologix Inc.) for elective AAA repair in a multicentric consecutive experience.

**Methods:**

All consecutive eligible patients submitted to endovascular aneurysm repair (EVAR) by Alto Endovascular AAA implantation will be included in this analysis. Patients will be submitted to EVAR procedures based on their own preferences, anatomical features, and operators experience. An estimated number of 300 patients submitted to EVAR with Alto stent graft should be enrolled. It is estimated that the inclusion period will be 24 months. The follow-up period is set to be 5 years. Full data sets and cross-sectional images of contrast-enhanced computed tomography scan performed before EVAR, at the first postoperative month, at 24 or 36 months, and at 5-year follow-up interval will be reported in the central database for a centralized core laboratory review of morphological changes. The primary endpoint of the study is to evaluate the technical and clinical success of EVAR with the Alto stent graft in short- (90-day), mid- (1-year), and long-term (5-year) follow-up periods. The following secondary endpoints will be also addressed: operative time; intraoperative radiation exposure; contrast medium usage; AAA sac shrinkage at 12-month and 5-year follow-up; any potential role of patients’ baseline characteristics, valuated on preoperative computed tomography angiographic study, and of device configuration (number of component) in the primary endpoint.

**Results:**

The study is currently in the recruitment phase and the final patient is expected to be treated by the end of 2023 and then followed up for 5 years. A total of 300 patients will be recruited. Analyses will focus on primary and secondary endpoints. Updated results will be shared at 1- and 3-5-year follow-ups.

**Conclusions:**

The results from this registry study could validate the safety and effectiveness of the new design of the Ovation Alto Stent Graft. The technical modifications to the endograft could allow for accommodation of a more comprehensive range of anatomies on-label.

**Trial Registration:**

ClinicalTrials.gov NCT05234892; https://clinicaltrials.gov/ct2/show/NCT05234892

**International Registered Report Identifier (IRRID):**

PRR1-10.2196/36995

## Introduction

### Background

An abdominal aortic aneurysm (AAA) is a dilatation in the lower part of the major vessel (aorta) that supplies blood to the body. The most accepted definition of AAA is based on a diameter of 3.0 cm or more, which is usually higher than 2 SDs above the mean diameter for men [1,2]. Over the last decades, the treatment options have changed. The traditional approach is represented by the open surgical repair [3,4]. As an alternative, the less invasive endovascular treatment has been proposed (endovascular aneurysm repair [EVAR]), which has become the first treatment of choice in patients with suitable anatomy [5,6]. EVAR represents a minimally invasive technique that has overcome some critical issues of open surgical repair such as higher intraoperative and perioperative risk; the necessity of general anesthesia; intensive care unit stay; and higher cardiac, pulmonary, and renal complications [7]. These advantages led to a constant increase in the AAA treatment feasibility, especially in elderly patients with a substantial number of comorbidities that could be treated with reasonable perioperative risks [8] and good early and mid-term outcomes [9] even in emergency settings [10].

Thirty years ago, Juan Parodi [11] developed the first prototype of endograft for EVAR, a handmade device made of a tube-shaped aorto-aortic graft sutured at each end to a balloon-expandable stent based on the design of radiologist Julio Palmaz. This device was implanted in a human body for the first time on September 7, 1990, in Buenos Aires, Argentina [12]. By 1994, the first commercially available device had been launched into the market [13]. Stent-graft material and design changed in various ways to improve conformability, reduce fracture, and minimize device migration rates [14]. Over the years EVAR has become an effective treatment for AAA in patients with challenging anatomy such as hostile neck and small access [15]. Tremendous success has been achieved owing to the continuous technological development that was able to overcome the previous limitations in EVAR applicability. Since 2010, the Ovation Abdominal Stent Graft System (Endologix Inc.) has offered a new concept of sealing, achieved by a network of O-rings filled by a polymer that can treat a great variety of difficult anatomies through a low-profile platform [16]. In the latest version of the stent graft, called Ovation Alto, the conformable O-rings with CustomSeal polymer have been repositioned near the top of the endograft, providing a seal just below the renal arteries. Very few papers highlighting the early and late outcomes of this new device, however, have been published. In this regard, this is intended to be the first multicenter prospective registry study on the implantation of the Alto stent graft in a large cohort of patients, who were also followed up for 5 years with a centralized core laboratory analysis of morphological changes. The aim of this study is to evaluate intraoperative, perioperative, and postoperative results in patients treated by the Alto stent graft (Endologix Inc.) for elective AAA repair in a multicentric consecutive experience.

### Device Under Investigation

The device under investigation represents the evolution of the low-profile Ovation Prime and iX endograft (Figure 1) [17]. The inflatable channels and the sealing rings, which are the most peculiar features of the predecessor endograft, remained unchanged. This ring network is still filled by a low-viscosity radiopaque polymer intraoperatively, which creates a customized sealing of the infrarenal neck.

Iliac limbs have also not changed and are deployed through a 12-15-Fr delivery system (outer diameter) with various lengths and diameters ranging from 80 to 160 mm and 10 to 28 mm, respectively. The new feature of Ovation Alto is the relocation of the proximal sealing ring at 7 mm from the main body fabric’s proximal edge. In the previous versions, this distance was 13 mm. The low-permeability graft material and the suprarenal 35-mm free-flow stent remained unchanged. It is still delivered via a flexible, hydrophilic-coated, low-profile delivery system (15-Fr outer diameter for all main body measures).

Another design improvement is the integration of a compliant balloon within the delivery system. The balloon is highlighted by a proximal radiopaque marker that coincides with the first sealing ring location, helping in the precise placement of the endograft.

The deployment of the device is performed in a 2-time maneuver (Figure 2). Initially, the lower part of the uncovered stent and the endograft module are deployed and expanded using the integrated, compliant balloon. The upper part of the bare stent remains temporarily undeployed. This system allows the repositioning of the endograft before the final deployment. After full stent-graft positioning and polymer injection, the balloon is advanced by 5-7 mm and re-inflated. This enables a more precise customization of the first sealing ring.

**Figure 1 figure1:**
[figure not shown]
Comparison between Ovation Alto endograft (left) and Ovation iX (right) endograft.

**Figure 2 figure2:**
[figure not shown]
A) Ovation Alto endograft model with the incorporated compliant balloon inflated. B) Intraoperative fluoroscopy with Ovation Alto semi-deployed with the incorporated balloon partially inflated. C) Intraoperative fluoroscopy with Ovation Alto endograft main body deployed, with O-rings polymer filled. The incorporated balloon is advanced of 5-7 mm and fully inflated.

Other minor modifications of the Ovation Alto design are as follows: (1) the inner diameter of the docking limb has been increased to 11 mm for all main body sizing; (2) a more definite web enriched the device bifurcation to avoid a prolapse of the contralateral limb during guide-wire access; (3) the aortic body limbs were offset by 5 mm to improve their identification during the procedure.

According to the current instruction for use, the following anatomical criteria are required [18]:

adequate iliac/femoral access compatible with vascular access techniques (femoral cutdown or percutaneous), devices, or accessories;a proximal aortic landing zone for the sealing ring 7 mm below the inferior renal artery;an aortic sealing zone consisting of healthy aorta defined asa lack of significant thrombus greater than 8 mm in thickness at any point along the aortic circumference at the level of 7 mm below the inferior renal artery;a lack of significant calcification at the level of 7 mm below the inferior renal artery;conicity <10% as measured from the inferior renal artery to the aorta 7 mm below the inferior renal artery;an inner wall diameter of no less than 16 mm and no greater than 30 mm at 7 mm below the inferior renal artery; andan aortic angle of ≤60°.a distal iliac landing zone:with a length of at least 10 mm andwith an inner wall diameter no less than 8 mm and no greater than 25 mm.

The contraindications for Alto stent-graft implantation according to the instruction for use are:

patients who have a condition that threatens to infect the graft andpatients with known sensitivities or allergies to the device materials (including polytetrafluoroethylene, polyethylene glycol–based polymers, contrast agents, fluorinated ethylene propylene, titanium, nickel, platinum, or iridium).

## Methods

### Study Patients

All consecutive eligible patients submitted to EVAR by Alto Endovascular AAA implantation will be included in analysis. Patients will be submitted to EVAR procedures based on their own preferences, anatomical features, and operators experience.

### Recruitment

An estimated number of 300 patients submitted to EVAR with Alto stent graft will be enrolled. It is estimated that the inclusion period will be 24 months. The follow-up period is set to be 5 years. Prior to enrollment into the clinical investigation, patients will be evaluated by their physician for inclusion criteria. Each patient’s medical condition should be stable, with no underlying medical condition that would prevent them from performing the required testing or from completing the study. Patients should be geographically stable, willing and able to cooperate in this clinical study, and remain available for midterm follow-up. Patients who do not wish to participate in this study can obtain the best available EVAR therapy as indicated; refusal to participate in this study will in no way affect their care at the institution. Inclusion and exclusion criteria are detailed in Textbox 1.

This study respects all the principles reported in the current version of Helsinki declaration (2013). AAA morphology will be assessed by OsiriX MD (OsiriX software; PIXMEO) on a computer (with Mac operating system) in a preoperative, contrast-enhanced, computed tomography angiographic (CTA) study. CTA must be performed with a biphasic acquisition protocol (unenhanced and contrast-enhanced scanning with a bolus tracking system) and reconstructions to 1-mm slices. All measurements (diameter, length, and angles) will be evaluated on a workstation with dedicated reconstruction software and center lumen line analysis and multiplanar reconstruction.

Inclusion and exclusion criteria.
**Inclusion Criteria**
Patients with abdominal aortic aneurysm who are scheduled for elective repair according to Endologix Alto endograft device’s instruction for use.Patient is willing to comply with specified follow-up evaluations at the specified times for the duration of the study.Patient is aged over 18 years.Patient, or his/her legal representative, understands the nature of the procedure and provides written informed consent prior to enrollment in the study.
**Exclusion Criteria**
Abdominal endovascular aneurysm repair performed in an urgent/emergent setting.Patients treated outside Endologix Alto endograft device’s instruction for use.Patients refusing treatment.Patients for whom antiplatelet therapy, anticoagulants, or antihypertensive drug are contraindicated.Patients with a history of prior life-threatening contrast medium reaction.Life expectancy less than the follow-up period.

A patient is considered enrolled in the study if he/she has full compliance with the study inclusion and exclusion criteria and after successful EVAR procedure at completion angiography.

Clinical data will be collected at patients’ enrollment, EVAR procedure, discharge, planned follow-ups (1-3 and 12 months after the procedure, yearly thereafter), unplanned or interim follow-ups, and patient death. CTA within 90 days, 24 or 36 months, and 5 years after the index procedure is mandatory. Duplex ultrasound scan will be performed at the same follow-up interval, and also at 12, 24, 36, and 48 months. A new CTA will be performed in case of unexpected events during follow-up. The follow-up protocol is based on the most recent European guidelines for the management of the AAAs [1].

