### Endpoint

The primary endpoint of the study is to evaluate the technical and clinical success of EVAR with Alto stent graft in short- (90-day), mid- (1-year), and long-term (5-year) follow-up periods. Technical success is defined as the correct graft deployment without any unintentional occlusion of the aortic visceral branches or both hypogastric arteries, with aneurysm exclusion confirmed by the intraoperative angiography, without signs of type I/III endoleak or conversion to open surgery or mortality. Clinical success includes successful deployment of the endovascular device at the intended location without death as a result of aneurysm-related treatment, type I or III endoleak, or graft infection or thrombosis, aneurysm expansion (>5 mm), aneurysm rupture, or conversion to open repair. Moreover, the presence of graft dilatation of 20% or more by diameter, graft migration, or a failure of device integrity will be evaluated.

The clinical and technical successes are defined “assisted” in case of unplanned endovascular procedures, or “secondary” if unplanned surgery is necessary [19].

The following secondary endpoints will be also addressed: (1) operative time; (2) intraoperative radiation exposure; (3) contrast medium usage; (4) AAA sac shrinkage at 12-month and 5-year follow-up; (5) any potential role of patients’ baseline characteristics, valuated on preoperative CTA, and of device configuration (number of component) in primary endpoint.

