### Data Collection and Analysis

Patient data will be captured electronically using a computer-based platform accessible to all investigators. Descriptive data summaries will be used to present and summarize the collected data. For categorical variables (eg, gender), frequency distributions and cross tabulations will be given. For numeric variables (eg, patient age), range, mean, median, and SD will be calculated. For all variables, a 95% CI for the relevant parameters of the underlying distribution will be calculated. For all time-dependent events, life tables will be calculated using the Kaplan-Meier estimate method for a period starting on the date of the procedure up to and including all follow-up visits. Stratification to risk factors will be performed and the log-rank test will be used to compare between the different outcomes; associated *P* values <.05 will be defined as significant.

All preoperative and follow-up CTAs were assessed and independently evaluated by 2 experienced vascular surgeons at core laboratory center. Disagreements will be discussed and resolved by consensus.

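### The instructions-for-use exclusion is worded by treatment received and settled after the procedure, so the course of the procedure can decide who enters the success-rate denominator

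*Protocol article*

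**What the plan says.** All references are to the Protocol article.

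- **Inclusion Criteria (Textbox 1).** The IFU condition concerns the plan: "Patients with abdominal aortic aneurysm who are scheduled for elective repair according to Endologix Alto endograft device’s instruction for use".
- **Exclusion Criteria (Textbox 1).** The IFU condition concerns the treatment given: "Patients treated outside Endologix Alto endograft device’s instruction for use". The exclusion before it is also worded by the procedure as done: "Abdominal endovascular aneurysm repair performed in an urgent/emergent setting".
- **Enrolment sentence, directly after the exclusion list.** A patient counts as enrolled on "full compliance with the study inclusion and exclusion criteria and after successful EVAR procedure at completion angiography". Compliance with the criteria is therefore settled once the procedure is over.
- **Recruitment.** "Prior to enrollment into the clinical investigation, patients will be evaluated by their physician for inclusion criteria". This names the inclusion criteria only, and enrolment itself comes after the procedure.
- **Study Patients.** The analysis is to cover every consecutive eligible patient undergoing EVAR with Alto, so whatever defines eligibility also defines the denominator.
- **Endpoint.** Technical success requires correct deployment of the graft. Clinical success requires deployment where it was intended. Both belong to the primary endpoint.

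**The concern.** A plan-based inclusion and a treatment-based exclusion do not select the same patients. They differ for the patient whose anatomy and plan are within the IFU but whose procedure departs from them. That patient satisfies the inclusion criterion, can have a successful completion angiogram, and still meets the exclusion as worded. Because enrolment is decided afterwards, the patient would simply never be enrolled.

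Selection would then depend on the course of the procedure, which is close to what the primary endpoint measures. The 90-day, 1-year and 5-year success rates would describe procedures that stayed on plan and not patients chosen for on-label Alto repair. The second group is the one a clinician deciding on treatment needs, and the one implied by the promise of a consecutive series. Nothing in the text ensures that sites would read the exclusion alike.

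This is distinct from the requirement of a successful completion angiogram for enrolment. That requirement leaves out procedural failures directly and is the larger problem. The IFU wording concerns patients whose angiogram was satisfactory.

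**Working it through.** **Step 1. The text.** The plan states no figure on this point, and 300 is given without a power or precision basis, so there is nothing to reproduce. Setting the criteria side by side:

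| Patient | Inclusion (as planned) | IFU exclusion (as treated) | Outcome as worded |
|---|---|---|---|
| Planned and treated within IFU | met | not met | can be enrolled |
| Planned outside IFU | not met | immaterial | not eligible |
| Planned within IFU, treated outside | met | met | not enrolled |

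The exclusion adds something to the inclusion criterion only in the third row. If it were a pure mirror of the inclusion criterion it would do no work.

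**Step 2. Can a procedure, as opposed to an anatomy, be off-label in this document?** The IFU items listed under Device Under Investigation are anatomical criteria and patient contraindications, all assessable beforehand. The Discussion, however, applies the term off-label to an operative act: deploying the sealing ring of the earlier Ovation iX 1 to 3 mm below the lowest renal artery instead of 13 mm. That was deliberate and with another device, so it proves nothing for Alto. It does show that a site could read the exclusion in this way.

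**Step 3. Direction and size.** Let q be the share of patients planned on-label who are left out because of a departure, S_on the success rate in the rest, and S_off the rate in those left out.

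- Success in all planned patients: (1 − q) × S_on + q × S_off.
- Success as reported: S_on.
- Overstatement: q × (S_on − S_off).

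The documents give none of these inputs, so all values below are assumptions.

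*Set A, S_on = 97%.* Overstatement in percentage points:

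| q | S_off 50% | S_off 80% | S_off 97% | S_off 100% |
|---|---|---|---|---|
| 1% | 0.47 | 0.17 | 0 | −0.03 |
| 5% | 2.35 | 0.85 | 0 | −0.15 |
| 10% | 4.70 | 1.70 | 0 | −0.30 |

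*Set B, in failure rates, 5% in the rest.*

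- q = 3%, failure 15%: 0.97 × 5% + 0.03 × 15% = 5.3%, against 5.0% reported (0.3 points).
- q = 10%, failure 30%: 0.90 × 5% + 0.10 × 30% = 7.5%, against 5.0% reported (2.5 points).

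**Step 4. Scale.** The 95% confidence half-width at N = 300 and 95% success is 1.96 × √(0.95 × 0.05 / 300) = 2.5 points. The upper corner of Set B is as large as the random error, and the lower corner is about an eighth of it (0.3 / 2.5). The planned confidence intervals would not reveal either.

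**Step 5. How many patients.** To enrol 300 when a share q is left out takes 300 / (1 − q) planned patients: 310 at 3% and 334 at 10%. That is about 10 to 34 patients outside the record.

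**The case against.** The strongest reply is that the exclusion merely restates the inclusion criterion. Every IFU item the article lists can be judged before the procedure, and other entries in the exclusion list are loose case descriptions too. Whether a misplaced ring or an adjunct makes a case one treated outside the IFU depends on the full IFU, which is not shown. A procedure that departs from the IFU midway is a scenario the article does not describe. This stands as a possible and perhaps intended reading. It does not remove the ambiguity, because the wording and the timing of enrolment permit the other reading.

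Three stronger readings are tempting, and the documents do not support them.

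- **Enrolled patients are removed after treatment.** No section provides for this. On the enrolment sentence the patient is never enrolled.
- **A core-laboratory re-reading excludes patients.** The article says "All preoperative and follow-up CTAs were assessed and independently evaluated by 2 experienced vascular surgeons at core laboratory center", and elsewhere gives that laboratory the review of morphological changes. The check of inclusion criteria belongs to the patient's physician. Nothing makes the laboratory's reading an eligibility test.
- **Patients in the assisted tier are lost.** The article says "The clinical and technical successes are defined “assisted” in case of unplanned endovascular procedures", which keeps and classifies such patients. It does not call those procedures outside the IFU.

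It is also fair to object that the size is wholly assumed and that the completion-angiogram condition is the greater fault. Both objections stand. Removing that condition alone would still leave the IFU exclusion open to being applied by treatment received.

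**Conclusion.** The point holds as a fault of wording and timing: the criteria as written let intraoperative events decide who is counted in the primary endpoint. An upward bias is conditional. It needs departures to occur, sites to apply the exclusion by treatment received, and those patients to fail more often. The last is plausible for two reasons. Correct deployment at the intended place is part of success, so a departure may itself be an endpoint failure. The Discussion also links inaccurate ring deployment with the previous device to early technical failure. A reader might infer that the reported rates will be inflated; the documents do not establish that.

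The size is unknown. It is nil if the two groups fare alike, 0.3 to 2.5 points under Set B, and up to 4.7 points at the extreme of Set A. The true figure may be small. The point is worth correcting because the remedy is cheap, but it is not critical and ranks below the completion-angiogram condition.

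**What to change.** 1. Reword the exclusion to: *Patients whose planned repair, on the site's preoperative CTA reading recorded before the procedure, is outside the instructions for use.*
2. Align the enrolment sentence that follows the exclusion list, so that IFU eligibility is fixed before the procedure.
3. Define the primary analysis set as every patient who met the inclusion criteria and no exclusion criterion on that preoperative assessment, and in whom Alto implantation was attempted.
4. Record intraoperative departures from the IFU with a flag, without excluding the patient.
5. Report the subset that was on-label as treated as a sensitivity analysis.

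Enrolment opened in January 2022, so sites should also be asked whether any patient has already been left out on this ground, and the number should be reported.

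The cost is one reworded criterion, one aligned sentence, one database flag and one extra table, with no additional imaging and no change to clinical care. The headline rate may be somewhat less favourable.

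### Enrolment is made conditional on a successful procedure, which contradicts the all-consecutive analysis population and, if followed, pushes technical and clinical success upward

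*Protocol article*

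**What the plan says.** The enrolment rule follows the exclusion criteria in the Recruitment part of the Methods. It requires "full compliance with the study inclusion and exclusion criteria and after successful EVAR procedure at completion angiography".

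The Endpoint section states: "The primary endpoint of the study is to evaluate the technical and clinical success of EVAR with Alto stent graft", at 90 days, 1 year and 5 years. Technical success has a deployment part, "correct graft deployment without any unintentional occlusion of the aortic visceral branches or both hypogastric arteries", and an angiographic and event part, "with aneurysm exclusion confirmed by the intraoperative angiography, without signs of type I/III endoleak or conversion to open surgery or mortality". On the other component, "Clinical success includes successful deployment of the endovascular device at the intended location". The same section labels success as assisted after unplanned endovascular procedures and as secondary after unplanned surgery.

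The Study Patients section sets a different population: "All consecutive eligible patients submitted to EVAR by Alto Endovascular AAA implantation will be included in analysis". The aim in the Background is "to evaluate intraoperative, perioperative, and postoperative results in patients treated by the Alto stent graft", in a consecutive multicentre experience. Under Recruitment: "An estimated number of 300 patients submitted to EVAR with Alto stent graft will be enrolled".

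**The concern.** Entry to the cohort depends on the outcome the cohort is meant to estimate. A failed deployment, a type I/III endoleak still present on the final run, a conversion or an intraoperative death would not ordinarily be called a successful procedure. Under the enrolment rule such a patient is outside the study. Under the Study Patients sentence the same patient is inside it and counts as a failure.

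If the enrolment rule is followed:

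- Technical success says little about how often the device fails at implantation.
- Clinical success at all three time points is a rate among patients whose procedure went well. The Kaplan-Meier curves have the same problem, because their clock starts on the procedure date while entry depends on the procedure's result.
- Operative time, radiation and contrast lose the uncorrected failures.
- The analysis of anatomy and device configuration against the primary endpoint loses many of its technical-failure events.

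The Discussion sets out to show that the device is safe and effective. It names inaccurate ring placement as a cause of early technical failure with the predecessor, and suggests that the new balloon helps. The failures that would test this argument are the ones the rule can remove. A statistical analysis plan could not repair this, because it cannot restore patients who were never enrolled. If centres read the two rules differently, the pooled rate would also mix denominators.

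**Working it through.** **What is reproducible.** The article gives 300 as an estimated number, with no expected success rate, precision or power behind it. There is no stated calculation to reproduce, and the point does not dispute the 300.

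**Rules side by side**

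| Patient | Study Patients rule | Enrolment rule |
|---|---|---|
| Good result at completion angiography | included | enrolled |
| Endoleak corrected before the completion run | included | can be enrolled; may be classed as assisted |
| Uncorrected type I/III endoleak, failed deployment, conversion, intraoperative death | included, as a failure | not enrolled |
| Unintentional branch occlusion, or death after the completion run | included, as a failure | unclear, since a successful procedure is not defined |

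**Notation.** Let t be the true technical success rate over all attempts, and L the share of technical failures that still pass the completion-angiography screen. The documents give neither. I assume t = 0.95, 0.97 and 0.99, and L from 0 to 0.5.

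**Step 1: observed technical success among the enrolled = t / (t + (1 − t)L)**

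- L = 0: t/t = 100% for any t. For 300/300 the exact lower 95% limit is 0.025^(1/300) = 0.988.
- t = 0.95, L = 0.10: 0.95/0.955 = 99.5%.
- t = 0.95, L = 0.25: 0.95/0.9625 = 98.7%.
- t = 0.95, L = 0.50: 0.95/0.975 = 97.4%.

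**Step 2: attempts behind 300 enrolled patients at L = 0 = 300/t**

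- t = 0.95: 315.8, so about 16 failures uncounted.
- t = 0.97: 309.3, about 9.
- t = 0.99: 303.0, about 3.

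**Step 3: clinical success over all attempts.** Assume 85% clinical success among the enrolled, and that each unenrolled failed attempt is a primary clinical failure. At L = 0 the all-attempts rate is t × 0.85.

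| t | All-attempts rate | Overstatement, 0.85 × (1 − t) |
|---|---|---|
| 0.95 | 80.75% | 4.25 points |
| 0.97 | 82.45% | 2.55 points |
| 0.99 | 84.15% | 0.85 points |

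These are upper ends for each t. If some failures pass the screen, the enrolled share is t + (1 − t)L and the gap narrows. At t = 0.95 and L = 0.25, 0.85 × 0.9625 = 81.8%, an overstatement of 3.2 points.

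**The case against.** The strongest reply is that the enrolment sentence may not govern the analysis. It defines who is enrolled, whereas the Study Patients sentence defines who is analysed and carries no success condition. Other text also points to entry before treatment: the data collection list puts enrolment ahead of the procedure, and the inclusion criteria select patients scheduled for elective repair. This stands in part. The bias is conditional on which rule is applied. The contradiction is not, because the article does not say which rule prevails or that unenrolled attempts are recorded.

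A reader might infer that technical success is fixed at 100% and so cannot be estimated at all. The documents do not support that. An endoleak corrected before the completion run can pass the screen, and some such cases may count as assisted, so unassisted success can still vary among the enrolled. Branch occlusion or a later death could also produce failures in enrolled patients. The 300/300 result is the extreme case. For the same reason, procedure time, radiation and contrast do not lose all their difficult cases, only those left uncorrected.

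A reader might also infer that consent can be taken once a good result is known, because it is required only before enrolment. That follows only by combining the consent criterion with the disputed sentence. The Recruitment text describes patients who decline as still receiving the best available repair, which places refusal before treatment. Late consent is therefore no part of this point.

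**Conclusion.** The point holds as an unresolved contradiction about the denominator of the primary endpoint, with upward bias if the enrolment sentence is the one followed. The direction does not depend on any assumed rate, provided that at least some technical failures are screened out. The size does: observed technical success of 97.4% to 100% for a true 95% (half to none of the failures passing), and clinical success overstated by at most about 0.9 points at a true technical success of 99% and 4.3 points at 95%. These figures rest on the assumed t, L and 85%, and on counting every failed attempt as a primary clinical failure. It should be corrected while recruitment is open, since later analysis cannot recover failures that were never recorded.

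**What to change.** 1. Reconcile the two passages by removing the successful-procedure condition from the enrolment sentence. Define enrolment as consent plus eligibility on the preoperative CTA, both before the procedure.
2. Define the analysis set as every enrolled patient in whom Alto implantation was attempted. Count failed deployment, conversion and intraoperative death as primary technical and clinical failures, and report assisted and secondary success separately, as the Endpoint section already provides.
3. Report the successful-procedure subset only as a labelled conditional analysis.
4. For the period since enrolment opened in January 2022, report at least the number of attempted but unenrolled cases per centre. Add patient-level data only where consent and ethics approval allow.

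The cost is a protocol amendment, a check of procedure logs at the centres, and consent and ethics handling for any past cases brought in. The 300 becomes 300 attempts, so no extra patients are needed. The reported success rate may be slightly less favourable. If centres already record every attempt, the change only corrects the wording.
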